## Abstract

**Background:**

Psychosocial problems such as depression, anxiety, and substance abuse are common and burdensome in young people, particularly those with long-term physical conditions such as asthma and diabetes. In New Zealand, “screening” for such problems is undertaken routinely only with Year 9 students in low-decile schools and opportunistically in pediatric settings using a nonvalidated and time-consuming clinician-administered Home, Education/employment, Eating, Activity, Drugs, Sexuality, Suicide/depression, Safety (HEEADSSS) interview. The Youth version, Case-finding and Help Assessment Tool (YouthCHAT) is a relatively new, locally developed, eTablet-based composite screener for identifying similar psychosocial issues to HEEADSSS. Based on individually validated screening instruments, it is self-administered within minutes. Preliminary testing has revealed its acceptability to young people, but further research is required to expand its modules to cover all HEEADSSS domains, to evaluate its acceptability for young people with and without long-term physical conditions, and to compare its effectiveness against HEEADSSS.

**Objective:**

Our aim is to (1) ascertain acceptability and utility of YouthCHAT for children with long-term physical illness and high school students, (2) validate three additional YouthCHAT domains against comparable HEEADSSS domains, and (3) compare the performance of YouthCHAT and HEEADSSS in the high school setting.

**Methods:**

During the first phase of the study, three additional YouthCHAT domains were codesigned with high school students. During the second phase of the study, the updated version of YouthCHAT will be administered to 30 young people with long-term physical conditions, and to 150 high school students either before or after HEEADSSS in the form of a randomized trial with counter-balanced design. Primary outcomes include comparability between HEEADSSS and YouthCHAT in detecting psychosocial issues, and time to administer; acceptability of YouthCHAT as an acceptable alternative or companion to HEEADSSS assessment; and the utility of YouthCHAT in helping streamline assessment processes.

**Results:**

Recruitment for the first phase of this project commenced in November 2016, and the phase will run from February to November 2017.

**Conclusions:**

If YouthCHAT is found to be acceptable to study participants and as effective as a HEEADSSS assessment, it could be an innovative and more efficient means of routine screening for common psychosocial health issues in young people with and without long-term physical conditions.

**Trial Registration:**

Australian New Zealand Clinical Trials Registry (ANZCTR) ACTRN12616001243404p; https://www.anzctr.org.au/Trial/Registration/TrialReview.aspx?id=371422 (Archived by WebCite at http://www.webcitation.org/ 6rmlEiM1L)

## Introduction

Psychosocial problems are a significant issue for young people in New Zealand, particularly those with long-term physical conditions. Recent figures indicate that 27% of high school students are affected by anxiety and depression [1], and at 18 years of age the prevalence of hazardous drinking exceeds 50%. New Zealand’s 2011 youth suicide rate was the second highest in the Organisation for Economic Co-operation and Development (OECD) [2]. As mental health and lifestyle issues often present in adolescence, it is important to intervene early so that problems do not become entrenched, leading to costly poor health and social outcomes [3-5].

Young people with long-term physical conditions are at even greater risk of psychosocial problems [6]. Depressive symptoms have been reported in as many as 40% of children with a long-term condition and socialization problems [7]. Anxiety has also been identified in children and young people with long-term physical conditions as an area of clinical significance [8]. The likelihood of such problems developing is related to young people’s internal ability to manage stress, which develops over time; family factors; and the impact of illness and treatment, particularly association with distress and pain [9].

The World Health Organization and New Zealand policies and programs all emphasize the importance of addressing youth mental health with appropriately targeted services and recognize the need for easily accessible services, including use of appropriate tools [10-12]. Young people want a greater say in how services are designed and delivered, and they expect services to be diverse, contemporary, and responsive. These requirements are echoed in many national policies including the New Zealand Mental Health Commission’s Blueprint II [13,14], the New Zealand Ministry of Health’s Rising to the Challenge 2012-2017 [15], Statement of Intent 2014-2018 [16], and the New Zealand Suicide Prevention Action Plan 2013-2016 [17].

Home, Education/employment, Eating, Activities, Drugs and Alcohol, Sexuality, Suicide/depression, Safety (HEEADSSS) assessment is a clinician-administered, interview-based assessment of youth that can identify mental health and substance use problems [18,19]. Currently, all Year 9 (13-14 year olds) students in low-decile schools (those with the highest proportion of students from low socioeconomic communities), and some attendees at primary care and pediatric services in New Zealand are screened for well-being via HEEADSSS assessment. While HEEADSSS assessment offers a straightforward, holistic, and gradual approach to assessing young people across many domains, it is a face-to-face assessment, not a screening tool. Drawbacks include its lack of validation for problem identification, the cost of resourcing, time required for its administration (up to 45 minutes), and variability of assessment depending on the skill and experience of the assessor. In many high schools, it takes a full school year and more than one school nurse to screen all Year 9 students (personal communication [name]). In pediatric settings around New Zealand, routine screening for psychosocial problems is not usually undertaken and HEEADSSS assessments are conducted by some medical and nursing staff in an ad hoc manner.

The Youth version of the electronic Case-Finding and Help Assessment Tool (YouthCHAT) [20,21] is a self-report screening tool that covers ten domains: smoking, drinking, recreational drug use (based on the Substances and Choices Scale [SACS]) [22], problematic gambling, depression (based on the Patient Health Questionnaire – Adolescent Version [PHQ-A]) [23], anxiety (based on the Generalized Anxiety Disorder scale, 7 item [GAD-7]) [24], sexual health, exposure to abuse, anger management, and physical activity. For each positive domain screened, there is a “help” question that asks participants if they would “like help today,” “want help, but another time,” or “don’t want help.” Responses to the “help” question support conversations between young people and their health providers about the issues they would like addressed, which facilitates shared decision making, with increased likelihood that real sustained changes will be made.

YouthCHAT provides summary reports to authorized school/health clinic staff plus a guide to stepped-care management from self-help through to secondary care. It is a rapid screening system (taking 5-15 minutes to complete) and can be conducted on any electronic device. YouthCHAT has a 14-year history of development in primary care, youth, and school clinics [20,21,25-31]. Recently, it was successfully implemented in a rural school clinic and favorably received by both young patients and clinic staff. Evidence indicates that students are more likely to disclose information about challenges they are facing through electronic means than an initial in-person assessment [32].

As a validated and rapid screening tool, YouthCHAT has the potential to overcome barriers associated with HEEADSSS assessment, while providing a similar holistic assessment of mental health and lifestyle issues. Additionally, as YouthCHAT collects and provides electronic data, the additional paperwork that HEEADSSS requires is not needed. YouthCHAT may be a more efficient screener and serve as a useful substitute or precursor to HEEADSSS assessment. YouthCHAT currently screens for all HEEADSSS domains except three: eating issues, conduct problems/bullying, and resilience/strengths. Additional screening questions to cover these domains have been added, based on those available in the existing literature, with appropriate wording advised by high school students, including those of Māori and Pacific Island descent via focus groups to ensure the updated version of YouthCHAT is appropriate for young people from all major ethnic groups in New Zealand.

The aims of this study are to (1) validate three additional YouthCHAT domains against comparable HEEADSSS domains, (2) ascertain the acceptability and utility of YouthCHAT for children with long-term physical illness and high school students, and (3) compare the performance of YouthCHAT and HEEADSSS in the high school setting.

We hypothesize that a version of YouthCHAT matched to HEEADSSS for all domains will be an acceptable alternative to a HEEADSSS assessment to both young people and the clinical staff conducting the screen. We further hypothesize that screening using YouthCHAT, followed up by a targeted or full HEEADSSS assessment where indicated, will be a much more streamlined and efficient system to enable identification and intervention of young people at risk.

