### Outcome Variables

The main study variables are (1) comparability (eg, is YouthCHAT at least as good or better than HEEADSSS assessment at detecting mental health and lifestyle issues among Year 9 youth? Is it a faster method of screening?), (2) acceptability (eg, is YouthCHAT content/format an acceptable alternative or companion to HEEADSSS assessment?), and (3) utility (eg, is YouthCHAT useful in helping to streamline assessment processes?).

Our primary outcome measures are (1) comparable detection rates for each domain for HEADSSS and YouthCHAT as measured by mental health or lifestyle issue “present” or “absent” (Tamaki sample only), (2) time taken to complete YouthCHAT and HEEADSSS screening (Tamaki sample only), and (3) acceptability and utility of YouthCHAT as assessed via feedback from staff and students/patients (Starship and Tamaki participants). Secondary outcome measures include differences in YouthCHAT versus HEEADSSS screening outcomes by gender and ethnicity.

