## Discussion

### Principal Considerations

If effective, YouthCHAT could offer an inexpensive, simple, scientifically valid, and acceptable vehicle for routine psychosocial screening in all young people in New Zealand high schools (not just those in Year 9 within low-decile schools) and all young people with long-term physical conditions (eg, during routine outpatient visits/annual check-up appointments in pediatric settings). It may also be useful to screen young people in multiple settings overseas.

On an individual level, early detection and intervention of mental health and substance misuse issues can have downstream benefits including improved physical health and better compliance with medical treatments, better engagement in education and subsequent employment, reduced youth suicide, and improved social relationships. Detecting and intervening in risky sexual behaviors can lead to a reduction in unwanted pregnancies and sexually transmitted infections. Dealing with bullying, physical and sexual abuse, and assisting youth with anger control will likely have significant psychosocial benefits. Helping youth make healthy eating choices and increase their physical activity can contribute to their physical and mental health and well-being, and reduce the incidence of conditions such as obesity and related illnesses. Although one other HEEADSSS-based electronic screener for young people (TickIT) has been evaluated for acceptability with this audience [34], no composite screener of this kind has yet been shown to be as effective in identifying psychosocial problems as face-to-face HEEADSSS assessment and there is no other gold standard for psychosocial screening. Evidence of efficacy of screening instruments is as relevant as evidence of acceptability, and this study hopes to demonstrate both for YouthCHAT.

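### Present/absent detection rates against HEEADSSS, which the article calls unvalidated and assessor-dependent, can show agreement but not validity or better detection

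*Protocol article*

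**What the plan says.** The Introduction gives as its first aim to "validate three additional YouthCHAT domains against comparable HEEADSSS domains". The Abstract lists the same aim second, and Study Design again speaks of validation. Under Outcome Variables, comparability is illustrated by the question "is YouthCHAT at least as good or better than HEEADSSS assessment at detecting mental health and lifestyle issues among Year 9 youth", and the first primary outcome is "comparable detection rates for each domain for HEADSSS and YouthCHAT as measured by mental health or lifestyle issue", recorded as present or absent under each tool.

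On the comparator, the Abstract describes current screening as "using a nonvalidated and time-consuming clinician-administered Home" and so on through the HEEADSSS domains. The Introduction adds "Drawbacks include its lack of validation for problem identification", lists "variability of assessment depending on the skill and experience of the assessor" as a further drawback, and says that HEEADSSS is an assessment rather than a screener. Principal Considerations states that "there is no other gold standard for psychosocial screening".

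The article describes no diagnostic interview, adjudication or second rater. Data Handling does provide a code that links each student's YouthCHAT record to the HEEADSSS file. Conclusion and Recommendations would, if the tools prove comparable and YouthCHAT is acceptable and faster, omit the routine HEEADSSS assessment after a negative YouthCHAT screen.

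**The concern.** Validating a tool means comparing it with something closer to the truth than the tool itself. Here the only yardstick is one whose own accuracy the article says is not established. With two fallible present/absent readings and no third source, neither tool's sensitivity or specificity can be identified. When the tools disagree about a student, the data do not say which is right. The Introduction cites evidence that students disclose more electronically than in person, so disagreement is foreseeable.

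Comparing marginal rates loses more information still, because two tools can flag the same proportion of students while flagging different students. At stake is the claim made for the three new domains and the proposal to omit HEEADSSS after a negative screen. That proposal turns on the students whom HEEADSSS flags and YouthCHAT does not, and a pair of detection rates does not show that group.

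**Working it through.** The article gives no accuracy figure for either tool. Its one power statement (144 participants, 90%) concerns administration time and has no bearing here. What follows is an illustration, not an estimate for this trial.

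**Inputs.** Prevalence p = 27%, from the Introduction; it refers to anxiety and depression, not to the new domains. p = 10% is an assumed alternative. All sensitivities (Se) and specificities (Sp) are assumptions.

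**Formulas.** Proportion flagged by a tool = p·Se + (1−p)·(1−Sp). For a perfect YouthCHAT judged against HEEADSSS, apparent sensitivity = p·Se / (HEEADSSS rate) and apparent specificity = (1−p)·Sp / (1 − HEEADSSS rate), with Se and Sp those of HEEADSSS.

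**1. A perfect YouthCHAT.** With HEEADSSS at 0.80/0.90:
- HEEADSSS rate = 0.27×0.80 + 0.73×0.10 = 0.289; YouthCHAT rate = 0.270.
- Apparent sensitivity = 0.216/0.289 = 74.7%; apparent specificity = 0.657/0.711 = 92.4%.

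The same formulas over a range of assumptions:

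| p | HEEADSSS Se/Sp | HEEADSSS rate | Perfect YouthCHAT rate | Apparent Se | Apparent Sp |
|---|---|---|---|---|---|
| 27% | 0.90/0.95 | 28.0% | 27.0% | 86.9% | 96.3% |
| 27% | 0.80/0.90 | 28.9% | 27.0% | 74.7% | 92.4% |
| 27% | 0.70/0.95 | 22.6% | 27.0% | 83.8% | 89.5% |
| 27% | 0.60/0.90 | 23.5% | 27.0% | 68.9% | 85.9% |
| 10% | 0.80/0.90 | 17.0% | 10.0% | 47.1% | 97.6% |

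In the 0.70/0.95 row, observed agreement is 0.8825 and chance agreement is 0.27×0.2255 + 0.73×0.7745 = 0.6263, so kappa = (0.8825 − 0.6263)/(1 − 0.6263) = 0.69. A flawless tool thus looks imperfect in every row, and its rate may lie above or below that of HEEADSSS.

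**2. A worse YouthCHAT.**
- Against HEEADSSS at 0.80/0.90, a YouthCHAT at 0.60/0.80 flags 0.27×0.60 + 0.73×0.20 = 0.308. It is inferior on both measures, yet its rate is higher (30.8% v 28.9%).
- Against HEEADSSS at 0.70/0.95, a YouthCHAT at 0.70/0.85 flags 0.189 + 0.1095 = 29.9%, against 22.6%. The whole excess is false positives (0.1095 v 0.0365 of students).

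**3. Similar rates, different students.** Take the first pair in step 2 and assume that the two tools err independently given true status.
- Flagged by both = 0.27×0.80×0.60 + 0.73×0.10×0.20 = 0.1442.
- HEEADSSS only = 0.289 − 0.1442 = 0.1448; YouthCHAT only = 0.308 − 0.1442 = 0.1638.

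The rates differ by 1.9 percentage points, but the tools disagree on 0.1448 + 0.1638 = 30.9% of students. In 150 students, HEEADSSS-only positives number 150×0.1448 ≈ 22. Of these, 150×0.27×0.80×0.40 ≈ 13 are true cases and 150×0.73×0.10×0.80 ≈ 9 are false positives. The trial would see the 22, if it tabulates them, but not the split.

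Steps 1 and 2 need no independence assumption; step 3 does.

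**The case against.** HEEADSSS is what every Year 9 student at the school receives and what YouthCHAT would partly replace, so comparing with it is a sensible pragmatic choice. The article says openly that no other gold standard exists. The new questions were drawn from existing validated tools and examined in focus groups, so the comparison is not their only support. All of this stands, and it supports agreement with current practice as a legitimate result. It does not support calling that result validation: noting the absence of another standard leaves HEEADSSS as the reference without limiting the claim.

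Several stronger readings are tempting but not supported:
- *That the aims commit the trial to showing YouthCHAT equal or superior.* That wording is an example question under Outcome Variables. The third aim is to compare performance, and the first primary outcome speaks of comparable rates, so that outcome needs no rewording on this account.
- *That the plan would read a disagreement in YouthCHAT's favour under one heading and against it under another.* No rule for disagreements is stated either way.
- *That the new domains are declared scientifically valid.* The remark in Principal Considerations is conditional and concerns the whole tool.
- *That over-detection is the main danger.* Under the article's proposal a positive domain leads to a targeted HEEADSSS assessment; a missed case after a negative screen gets no such check.

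The accuracies used in the working are assumed and the prevalence belongs to other domains, so the figures show what can happen, not what will.

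**Conclusion.** The point holds in this form. The article claims validation, and asks about better detection, against a comparator that it describes as unvalidated and assessor-dependent, with no independent reference. Per-domain present/absent rates can support a statement about similar rates, and paired data a statement about agreement; neither establishes validity or better detection. Under assumed accuracies at 27% prevalence the ranking by rate can reverse: 27.0% for a perfect YouthCHAT and 30.8% for an inferior one, against 28.9% for HEEADSSS. The direction depends on assumptions that the trial cannot check.

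A reader might infer that the comparison is uninformative; it is not. Agreement with current practice is worth knowing, and the conclusion on administration time does not depend on this point.

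**What to change.** 1. Replace validation by agreement with HEEADSSS, named as current practice, in the aim (Abstract and Introduction) and in Study Design. Reword the example detection question under Outcome Variables in the same way.
2. State that a higher YouthCHAT detection rate will not by itself be read as better detection.
3. For each domain, report the paired 2×2 table with both discordant cells and an agreement measure, using the student-level matching in Data Handling. The HEEADSSS-only cell needs particular attention, because the proposal to omit HEEADSSS after a negative screen depends on it.
4. Use help responses and referrals, if at all, only to describe discordant students. A help response records a wish for help and is asked only for YouthCHAT-positive domains, and referrals follow from the positive screens themselves. Neither is a reference standard.

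The cost is a weaker headline claim and one extra table. No new data, participants or visits are needed.

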## Methods

### Study Design

We will use a mixed-methods participatory action research approach to development and validation of a YouthCHAT mapped to all HEEADSSS domains, and assessment of the acceptability and utility of YouthCHAT at a tertiary pediatric hospital and a low-decile high school. A randomized controlled trial (RCT) with counterbalanced design will be conducted at the high school to assess the comparability of YouthCHAT and HEEADSSS.

### Participants and Recruitment

During the first phase, up to 20 senior students aged 16-18 years from Tamaki College, a low-decile high school in Auckland, New Zealand, were invited to participate in focus groups to update YouthCHAT via flyers sent to their school. These students were chosen as they were all able to give their own consent.

During the second phase, approximately 150 Year 9 students (aged 13-14 years) from the same high school will be invited to participate in the RCT and school-based acceptability evaluation via letters will be sent to their parents. Parents may use a reply-paid form to opt out of the study if they do not wish their children to participate. However, regardless of this, all students will receive mandatory HEEADSSS assessments (as is routine for all students in this class). Students who choose to participate in the study will be randomly assigned to one of the two conditions (YouthCHAT followed by HEEADSSS assessment or HEEADSSS assessment followed by YouthCHAT) via a computer-generated random numbers table, with resulting lists provided to clinic staff. Sampling will be consecutive until all enrolled students have completed assessment. All screening will take place in the student health clinic on a desktop computer. A subset of 32 students will be invited to participate in four focus groups, and four school staff (nurses and counsellors) will be invited to complete semistructured interviews on the acceptability, utility, and comparability of YouthCHAT and HEEADSSS assessment. This age group of participants was chosen as it matches the age group of students who routinely receive HEEADSSS assessments in New Zealand low-decile schools.

Also during the second phase, 30 young people aged 13-18 years with long-term physical conditions (eg, diabetes, asthma, cystic fibrosis and congenital heart disease) attending outpatient clinics at Starship Children’s Hospital, a tertiary pediatric hospital will be invited to participate in the study via flyers disseminated by clinic staff. Following individual or parental consent (and personal assent), they will be asked to complete YouthCHAT and a postconsultation survey to assess its acceptability and utility. This age group of participants has been chosen as it matches the age range to which YouthCHAT is targeted. Pediatricians and specialist nurses who have conducted these consultations will be also invited to undertake a short semistructured interview to provide a clinical perspective on the use of YouthCHAT in a pediatric setting.

